#### **13.4.4 Effect on Sexual Function**

Analysis of the Sexual Adjustment Questionnaire (SAQ) will be performed on all patients that complete baseline questionnaires. The SAQ has five subscales; desire, activity level, arousal, orgasm, and satisfaction, that will be used to assess the effect of treatment, changes in serum testosterone, and other patient characteristics on patients' perception of quality of sexual function. The SAQ will be administered pretreatment, post radiotherapy, every three months for the first year of follow-up, and every four months for the second year of follow-up. The analysis will utilize analysis of variance, and repeated measures analysis of variance to examine differences in treatments. The SAQ will be examined for responsiveness in follow-up and correlation to changes in serum testosterone. Analysis of SAQ responses by subgroups will be undertaken for groups with sufficient sample size. Functional status, the ability to have an erection, will be measured with a 'yes/no' response at baseline and at each follow-up. A two-sample proportion test with a different standard deviation will be used at the significance level of 0.05.

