The Sexual Adjustment Questionnaire (SAQ) has five subscales; desire, activity level, arousal, orgasm, and satisfaction, that will be used to assess the effect of treatment, changes in serum testosterone, and other patient characteristics on patient's perception of quality of sexual function. The SAQ will be applied pretreatment, post radiotherapy, every three months for the first year of follow-up, and every four months for the second year of follow-up. Because it is unknown when a critical or defining change in sexual function occurs or remains stable all eight follow-up questionnaires are required and necessary for comparison of groups. Submission of the initial SAQ on RTOG 91-16 was 90% and 67% on RTOG 90-20. The submission of the follow-up questionnaires ranges from 40-90%.

This study should have sufficient numbers of patients completing the two-year follow-up SAQ to find a difference of at least one in the mean responses between groups for any of the five subscales. The estimated variance and completion rates will impact the required sample size. Because there is no reliable estimate of the SAQ response variance and completion rates will vary these parameters will be estimated after 200 patients have been randomized to this trial. These estimates will be utilized to determine whether additional patients will be accrued to the SAQ component. The results of this analysis will be presented to the Data Monitoring Committee (DMC).

Functional status, the ability to have an erection, will be measured with a 'yes/no' response at baseline and at each follow-up. It is assumed that at least 50% of all patients will enter the study with the ability to have an erection and 70% of these patients on the RT alone arm will retain this function. If 300 patients that enter the trial with the ability to have an erection are analyzable at 2 years, then this trial will have at least 80% statistical power to detect at least a 15% (*absolute*) reduction in the retention of function in the RT+TAS arm, testing at the 0.05 (*one-sided*) level.

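### The SAQ analysis names repeated measures ANOVA for every man with a baseline form, but in its classical form that method uses only men with all eight follow-ups, and the cited return is 40-90%

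*Protocol*

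**What the plan says.** Protocol section 13.4.4 fixes both the set and the method, and section 13.4 repeats them. The set: "Analysis of the Sexual Adjustment Questionnaire (SAQ) will be performed on all patients that complete baseline questionnaires". The method: "The analysis will utilize analysis of variance, and repeated measures analysis of variance to examine differences in treatments". Besides the baseline form, the schedule in 13.4.4 is "post radiotherapy, every three months for the first year of follow-up, and every four months for the second year of follow-up".

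Section 13.3 adds three things.

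- On the forms, it says that "all eight follow-up questionnaires are required and necessary for comparison of groups".
- On return rates, it says "Submission of the initial SAQ on RTOG 91-16 was 90% and 67% on RTOG 90-20" and then "The submission of the follow-up questionnaires ranges from 40-90" (per cent). It does not say whether that range runs across visits, across studies or both.
- On planning, the aim is "to find a difference of at least one in the mean responses between groups for any of the five subscales" among men who complete the two-year form. No standard deviation, power or sample size is given for this. Instead: "Because there is no reliable estimate of the SAQ response variance and completion rates will vary these parameters will be estimated after 200 patients". The results of that check go to the Data Monitoring Committee.

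Section 11.3.12 is marked as discontinued on 7/1/97, and the form list in section 12.0 gives the same date for the end of quality-of-life assessments. Section 13.4.4, part of a section last dated 7/14/08, still describes SAQ administration in the future tense.

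**The concern.** Three statements do not fit together: an analysis set defined by the baseline form alone, a comparison said to need eight follow-up forms, and a cited follow-up return that can be as low as 40%. Classical repeated measures ANOVA works on complete profiles, so a man who misses one of the eight visits leaves the analysis. Plain ANOVA, the other named method, can be run visit by visit, but then each comparison covers only the men who answered at that visit. No section says how a man with an incomplete profile stays in the comparison over time.

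Both analyses can be biased if returning the form is related to sexual function. That is plausible for a questionnaire on this subject. Section 1.6 cites impotency of 25-30% after radiation alone and at least 80% with hormonal therapy, so any such link could act differently in the two arms. Section 1.6 also says survival gains must be weighed against this loss, and sexual function is a secondary objective (2.2.3) and endpoint (13.2.2.9).

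**Working it through.** **Number of forms.** From the schedule: 1 after radiotherapy + 12/3 = 4 in year 1 + 12/4 = 3 in year 2 = 8. This reproduces the eight stated in 13.3.

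**Inputs.** Follow-up return p = 0.40 to 0.90 (section 13.3), with the midpoint 0.65 added. The documents give no within-man correlation of returns, so ρ is an assumption shown over its range. All shares below are among men with a baseline form.

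**Share of men with all eight forms**

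- Independent returns: p^8.
- Correlated returns (beta-binomial): the product over i = 0 to 7 of (p·s + i)/(s + i), with s = (1 − ρ)/ρ.
- Upper limit (the same men always answer): p.

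| Return at every visit | Independent | ρ = 0.5 (assumed) | Upper limit |
|---|---|---|---|
| 90% | 0.90^8 = 43.0% | 75.6% | 90% |
| 65% | 0.65^8 = 3.2% | 34.4% | 65% |
| 40% | 0.40^8 = 0.07% | 12.7% | 40% |

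**Where half the men are kept.** With independent returns this needs p = 0.5^(1/8) = 91.7% at every visit, just above the top of the cited range. With correlated returns, half are kept once ρ exceeds about 0.06 at 90% return, 0.40 at 80% and 0.75 at 65%. At 40% return it is impossible.

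**If the range is a spread across visits.** Suppose return falls evenly from 90% to 40% over the eight visits. The product of the eight rates is 2.4% under independence. Under any dependence, the complete share cannot exceed the lowest visit's rate, 40%.

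**Plain ANOVA at one visit.** It uses the fraction p of men who answered at that visit, so 40% to 90%. It does not need eight forms, but it ignores the earlier scores of the men who are absent.

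**Discontinuation.** The eighth form falls about two years into follow-up. If 7/1/97 ended collection for everyone, a man entered later than about mid-1995 cannot have all eight forms, however willing he was to answer.

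**The case against.** The strongest reply is that the protocol nowhere says complete cases only. Its stated set is all men with a baseline form, which points the other way. Repeated measures ANOVA is a broad label, and some implementations accept incomplete profiles. The remark that eight forms are necessary follows a statement that the timing of change is unknown, so it justifies collecting the forms and is not an exclusion rule. Handling of missing forms may sit in an analysis plan that is not shown. All of this stands, and it rules out saying that the plan prescribes deletion. It does not defend the choice of method: the method is named twice, and its classical form cannot deliver the stated set.

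Second, 40-90% is an undefined range beside earlier-trial figures, and 13.3 plans a check of completion after 200 patients. This also stands. The range is not a forecast for each visit of this trial. It is, however, the only follow-up figure given, and the check is meant to decide whether more men join the SAQ component. It does not change the analysis.

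Third, the stated target concerns men with the two-year form, and a single-visit ANOVA there does not need eight forms. Potency, the main worry in 1.6, has its own yes/no item and its own test. Both points are correct. They limit the issue to the SAQ and mainly to its comparison over time.

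A reader might infer more: that most men will be lost, that those kept are a selected group, and that the effect of androgen suppression will be understated. The documents do not support this. The first depends on the return rate and on ρ, and it fails near 90% return with modest correlation. For the other two, the protocol has no data on who returns forms, and any size put on the bias would rest on invented dropout rules.

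**Conclusion.** The point holds in a conditional form. The named repeated measures method, read classically, conflicts with the stated analysis set as soon as forms are missing. The share of men it would use runs from 0.07% to 43% over the cited range if returns are independent, and is at most 40% if the range is a spread across visits. It can exceed half at about 90% return with correlated returns. These figures assume complete-profile analysis, which the protocol permits but does not require.

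Visit-by-visit ANOVA avoids the complete-profile loss but not the risk of bias from non-return related to sexual function. That risk is plausible and unshown. If the 7/1/97 stop applied to men already on study, calendar time adds a further cause of incomplete profiles; the protocol does not settle whether it did. The issue is confined to one secondary endpoint and does not touch the overall survival analysis.

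**What to change.** In sections 13.4 and 13.4.4, replace repeated measures ANOVA with a likelihood-based mixed model for repeated measures: arm, visit and arm-by-visit terms, unstructured within-man covariance, and every returned SAQ from men with a baseline form. Report the arm difference at two years with its 95% confidence interval, and set out return rates by arm and visit beside it. Add a sensitivity analysis for informative non-return. Reconcile 13.4.4 with the 7/1/97 discontinuation by stating whether men already enrolled went on completing forms, and separate forms missing for that reason from forms not returned.

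The cost is wording and standard software, with no new patients or data. The model still assumes that missing forms are explained by scores already observed. If men stop answering because of a loss they have not yet reported, it can be biased too, which is why the sensitivity analysis is needed.

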#### **13.4.5 Interim Report to Monitor the Study Progress**

Interim reports with descriptive statistics will be prepared twice per year until the initial paper reporting the treatment results has been submitted. In general, the interim reports will contain information about the patient accrual rate with a projected completion date for the accrual phase, the compliance rate of treatment delivery with the distributions of important prognostic baseline variables, and the frequencies and severity of the adverse event by treatment arm. The interim reports will not contain the results of the treatment comparisons with respect to the primary endpoint and secondary endpoints.

### **13.5 Inclusion of Women and Minorities (4/1/96)**

In conformance with the National Institute of Health (NIH) Revitalization Act of 1993 with regard to inclusion of women and minority in clinical research, we have considered the possible interaction between race and treatments. Analysis of three prior RTOG studies failed to show such a significant difference and so this study was not designed to test for treatment differences within race. A sensitivity analysis was done with the targeted sample size by racial groups in testing for treatment differences. If 88% of the patients recruited in this study are white/other, the statistical power to detect a reduction by 33% in the failure rate (defined in Section 13.2) is .86. If 12% of the patients recruited in this study are Afro-Americans, the statistical power to detect a reduction by 33% in the failure rate is .20.

The analysis for reporting the initial treatment results will include treatment comparisons within each race for the failure rate (defined in Section 13.2) and for overall survival.

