## **13.3 Sample size and accrual (7/14/08)**

**As of July 1, 1997, the sample size is 1980 (See section 13.7).**

*TAS* is known to lower PSA but time to initial PSA failure may not be a good indicator of ultimate clinical outcome. If neoadjuvant *TAS* is successful, there should ultimately be a positive impact on cause-specific survival. Because of the expected mortality due to other causes in this population, an improvement in cause-specific survival may be difficult to detect if overall survival were used as the primary endpoint. Clearly identifying deaths due to prostate cancer is difficult because metastasis is usually to the bone rather than to a vital organ.

The primary endpoint for this trial upon which sample size is based is defined to be closely associated to death due to prostate cancer. Review of causes of death by the study chair will be necessary.

The following will be considered treatment failures:

1. Death certified as due to carcinoma of the prostate.
2. Cancer associated death.
3. Death due to complications of treatment irrespective of the status of the cancer.
4. Progressive metastatic disease while on any antitumor therapy.
5. Rising PSA while on any antitumor therapy.

Average failure rates were obtained from other datasets with the recognition that they may not be identical with what might be expected from this population.

Death rate: The death rate from early stage prostate patients from RTOG 77-06 had an average annual death rate of 0.045. Fourteen of the 46 reported deaths were categorized as due to prostate cancer. The prostate cancer death rate and other cause death rate were found by multiplying 0.045 by 14/46 and (46-14)/46.

Rate of first failure: This was taken to be 0.12 (*communication [name]*).

Rate of second failure while on hormonal therapy: This was taken to be 0.24 (*communication [name]*).

The goal of the trial is to be able to detect a lowering of the failure rates by 33% with 90% power using a two-sided test. Using methods described by Lakatos, **a total of N=670 patients are required** to be accrued uniformly over three years and followed for three additional years before final analysis of treatment failure. This includes an estimate of 10% unevaluable patients. The expected numbers of events on the two arms at the time of final analysis are 71 and 39.

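### Section 13.5 raises a race-by-treatment interaction but commits only to separate comparisons within each race, which at the stated powers often split even if the effect is the same

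*Protocol*

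**What the plan says.** Section 13.5 (dated 4/1/96) opens from the interaction question: "we have considered the possible interaction between race and treatments". It reports that three earlier studies by the group showed no significant difference, "so this study was not designed to test for treatment differences within race". It then gives power by racial group. For the larger group: "If 88% of the patients recruited in this study are white/other, the statistical power to detect a reduction by 33% in the failure rate" is put at .86. For the smaller: "If 12% of the patients recruited in this study are Afro-Americans", then "the statistical power to detect a reduction by 33% in the failure rate is .20". The section closes with a commitment: "The analysis for reporting the initial treatment results will include treatment comparisons within each race for the failure rate", and for overall survival as well.

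Nothing else in the protocol examines treatment by race. Sections 13.4.1 and 13.4.2 list race only among the covariates to be adjusted for.

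Section 13.5 points twice to section 13.2 for the definition of the failure rate. Section 13.2, revised 7/14/08, now lists overall survival as primary endpoint and nine secondary endpoints, none of them called a failure rate. The five-item definition of treatment failure is in section 13.3, next to the design it served, which used a two-sided test: "The goal of the trial is to be able to detect a lowering of the failure rates by 33% with 90% power using a two-sided".

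**The concern.** Whether an effect differs by race is a question about the difference between two effects. Two separate comparisons, one in about 88% of the patients and one in about 12%, do not test that difference. They differ greatly in precision, so one can reach significance and the other miss it although the underlying effect is the same.

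The stake is interpretation. A report showing significance in white/other patients and none in Afro-American patients invites the conclusion that androgen suppression does not help Afro-American men, when the data may be fully compatible with the overall effect. An adjustment covariate for race does not address this, because it assumes a common treatment effect.

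The stale reference adds a smaller problem: a reader who follows it does not reach a definition for the first of the two by-race comparisons.

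**Working it through.** **Inputs**
- Section 13.5: shares 88% and 12%; powers .86 and .20 for a 33% reduction.
- Section 13.3: 33% reduction, 90% power, two-sided.
- Section 13.8.2 (1997 design): 33% reduction in prostate cancer death, two-sided 0.05, 90% power. Section 13.4: 261 such deaths.
- Section 13.4.1 (current design): 716 deaths, hazards 0.0501 and 0.0639, 90% power, one-sided 0.025.
- Section 13.8.1: an average 11% reduction in death from all causes.
- Assumptions: each race's share of events equals its share of patients; 1:1 allocation within race.

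**1. Reproducing the stated powers.** The expected log-rank statistic scales with the square root of the event share. For 90% power at two-sided 0.05 it is 1.960 + 1.282 = 3.2415 overall.
- White/other: Φ(√0.88 × 3.2415 − 1.96) = Φ(3.041 − 1.96) = 0.860.
- Afro-American: Φ(√0.12 × 3.2415 − 1.96) = Φ(1.123 − 1.96) = 0.201.

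Both stated figures are confirmed. One-sided 0.05 would give 0.864 and 0.264, so the stated pair is two-sided 0.05.

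**2. Pattern of results if the effect is the same in both races.** The groups share no patients, so the two tests are independent.

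| Significant in | Calculation | Probability |
|---|---|---|
| White/other only | .86 × .80 | 0.688 |
| Afro-American only | .14 × .20 | 0.028 |
| Exactly one race | 0.688 + 0.028 | 0.716 |
| Both | .86 × .20 | 0.172 |
| Neither | .14 × .80 | 0.112 |

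**3. Carry-over to the current design.** The hazard ratio is 0.0501/0.0639 = 0.784, and power is Φ(½√d × |ln HR| − 1.96). With d = 0.88 × 716 = 630 the power is 0.863; with d = 0.12 × 716 = 86 it is 0.203. White/other only: 0.863 × 0.797 = 0.688. Exactly one race: 0.716. The 1997 design (261 deaths, hazard ratio 0.67) gives 0.859 and 0.201. All three agree because each design has about 90% overall power.

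**4. Where the result stops holding.** Take the 11% reduction, hazard ratio 0.89, with 716 deaths. Overall power is Φ(½√716 × 0.1165 − 1.96) = Φ(1.559 − 1.96) = 0.34. Within-race powers are 0.309 and 0.078.
- White/other only: 0.309 × 0.922 = 0.29.
- Afro-American only: 0.078 × 0.691 = 0.05.
- Neither: 0.691 × 0.922 = 0.64.

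By overall power, a split (exactly one race) compares with neither as follows: 0.461 against 0.493 at 50%; 0.536 against 0.401 at 60%; 0.715 against 0.112 at 90%. With no effect at all, apparent benefit in exactly one race occurs with probability 2 × 0.025 × 0.975 = 0.049.

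**5. What an interaction test offers.** At two-sided 0.05 it would falsely signal a race difference 5% of the time under a common effect. With 716 deaths the standard error of the difference in log hazard ratios is √(4/630 + 4/86) = 0.230. If the hazard ratio were 0.784 in white/other and 1 in Afro-American patients, the standardised difference is 0.243/0.230 = 1.06 and power is about 18%. For 80% power the ratio of hazard ratios must be about exp(−2.80 × 0.230) = 0.52.

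**6. What the interval shows.** On 86 deaths the standard error of the log hazard ratio is 2/√86 = 0.216. An estimate of 0.78 would have a 95% CI of about 0.51 to 1.20. That is visibly compatible with the overall effect, which a bare non-significant p-value does not show.

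**The case against.** The strongest reply is that the protocol has not committed the error. It speaks of comparisons, sets no within-race significance level and gives no rule for drawing conclusions by race. It discloses the .20 power, which warns that a null result in the smaller group means little. Committing to one analysis does not exclude another, and an analysis plan that is not shown here could add an interaction term without contradiction. This stands in part. A reader might infer that the protocol makes within-race significance the test of whether the effect differs; the text does not say so, and the harm arises only if the results are read that way.

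A reader might also infer that a false one-race result is simply the most likely outcome. The documents do not support that unconditionally, because section 13.8.1 itself translates the hypothesised effect into an 11% all-cause reduction, at which significance in neither group leads.

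Nor is the failure rate left undefined. Its definition survives in section 13.3, so the pointer is stale rather than empty.

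Finally, the interaction test is weak, so adding it alone would settle little.

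What remains is that section 13.5 raises an interaction question and then names an analysis that does not answer it. That is a choice the protocol has made, not merely detail left open.

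**Conclusion.** The point holds in limited form. The protocol commits to separate comparisons within each race and names no treatment-by-race analysis. If the effect is the same in both races and near the design value, and each race is read by its own p-value, significance in white/other only has probability about 0.69 and a split of either kind about 0.72. This rests on event shares matching the 88/12 split and on overall power near 90%. It does not hold under no effect or a much smaller one.

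The primary test, its significance level and the 716-death target are unaffected. The matter concerns how by-race results will be reported and read, and it is worth correcting because the correction is small. The reference to section 13.2 is out of date, and the .86 and .20 belong to the superseded 33% failure-rate design. Similar values under the current design follow only because it too has 90% overall power, for a 21.6% reduction in death.

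**What to change.** In section 13.5:

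1. Report the overall survival hazard ratio with its 95% CI in each racial group, together with one treatment-by-race interaction term in the Cox model of section 13.4.1.
2. State that within-race p-values will not be used to conclude that the effect differs by race.
3. Replace the failure rate and its pointer to section 13.2 with a named current endpoint.
4. Mark .86 and .20 as figures for the superseded failure-rate design, or restate them for overall survival (0.863 and 0.203 on the assumptions above).

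The cost is one model term and a few sentences. By-race reporting is kept, and no procedure for patients changes. The downside is the low power of the interaction test, about 18% even if benefit were wholly absent in the 12% group. A non-significant interaction must therefore not be read as proof of equal effects, and the confidence intervals should carry the message.
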